#### Secondary outcome measures

Secondary outcome measures of symptomology, neurocognition, static and dynamic balance, and central sensorimotor integration are provided in Table 3.

**Table 3 Tab3:** List of all outcome measures by domain

Domain Tested	Test	Description	Clinical Outcomes	Instrumented Outcomes
Symptomology	Dizziness Handicap Inventory (DHI) [54]	Questionnaire about dizziness while performing various tasks	Total symptom score	-
	Post-Traumatic Stress Disorder (PTSD) Checklist [55]	List of problems and complaints people have in response to stressful life experiences	Total symptom score	-
	Pain Location Inventory (PLI) [56]	Questionnaire about presence and location of pain	Total symptom score	-
	SIQR Symptom Questionnaire [57]	Rates symptoms on a sliding scale	Total symptom score	-
	Sport Concussion Assessment Tool 3 (SCAT3) Symptom Questionnaire [58]	Rates 22 symptoms on a scale from 0 to 6	Total symptom score	-
	Becks Depression Inventory (BDI-II) [59]	Questions regarding depression and personal emotions	Total symptom score	-
	Short Form 36 (SF-36) [60]	36 questions about daily living and how symptoms have or have not changed over time	Total symptom score	-
	Neurobehavioral Symptom Inventory (NSI) [61]	Rates common symptoms associated with TBI	Total symptom score	-
Neurocognition	Automated Neuropsychological Assessment Metrics (ANAM) [62]	Computerized battery of neurocognitive tests	Individual component scores, Summary score	-
Reaction Time	Clinical Reaction Time Test [63]	Consists of dropping a rod attached to a weighted disk and measuring the distance the rod falls before being caught	Average distance the disk falls	-
Static Balance	Modified BESS [58]	20 s of stance with feet together, on one leg, and in tandem stance	Subjective error count	Measures of sway: RMS, jerk, total power, Mean distance, sway area
	Clinical Test of Sensory Organization and Balance (CTSIB) [64]	60 s of stance in 4 conditions: eyes open on firm ground, eyes closed on firm ground, eyes open on foam, eyes closed on foam	Number of conditions completed	Multi-scale complexity (entropy)
Dynamic Balance	Single-task gait	Walking at a comfortable pace down and back in a 16 m hallway for 16 times.	Gait speed, time to complete	Mediolateral trunk sway, Phase-coordination index, stride length, stride variability, nonlinear local dynamic stability
	Dual-task gait	Walking at a comfortable pace down and back in a 16 m hallway for 16 times while verbally responding to an auditory stroop cue	Change between single-task and dual-task gait speed	Change between single-task and dual-task instrumented outcomes
	Turning gait	Walking at a comfortable pace around a marked course 12 times	Average time to complete the course	Head-trunk-lumbar roll angular velocity, head-trunk-lumbar-foot yaw velocity, coordination of head-trunk-lumbar-foot reorientation
	Fast turning gait	Walking at a fast pace around a marked course 4 times	Change in time to complete course between comfortable and fast walking speeds	Change in turning gait instrumented measures between comfortable and fast walking speeds
Central Sensorimotor Integration	Sensory Organization Test (SOT) [65]	Calculates visual, proprioceptive, and vestibular ratio scores based on sway under varying sensory conditions	Visual, proprioceptive, and vestibular ratio scores	-
	Novel CSMI Test [22]^a^	Quantifies sway response to pseudorandom stimuli by calculating sensory weighting and neural controller parameters	-	Parameters defined in Table 2
Daily Activity	At-home activity monitoring^b^	Uses an inertial sensory worn daily to quantify the activity level	-	Activity level, number of steps per day, number of turns per day

^a^Primary outcome measure for Study 1 and Study 2

^b^Secondary outcome measure for Study 2 only

#### Static and dynamic balance testing

Subjects will be instrumented with body-worn inertial sensors during the performance of static and dynamic balance tests. Five synchronized wireless Opal inertial sensors (APDM, Inc., Portland, OR) will be affixed to the participants’ head, sternum, lumbar, left and right feet using elastic straps. Data will be collected at 128 Hz and transferred to a laptop for automatic generation of gait and balance measures by Mobility Lab software [48] and additional analysis of the raw time-series data. Specific tests and instrumented measures of static and dynamic balance are presented in Table 3.

#### Clinical testing for classification and covariates

To classify mTBI participants as with or without vestibular dysfunction, standard vestibular testing will be performed as described in Table 4. Clinical tests to examine potential covariates of sensory loss will also be included at the initial visit in Study 1.

**Table 4 Tab4:** List of clinical sensory and vestibular tests for classification and covariates / comorbidities of primary and secondary outcomes

Domain Tested	Test	Description	Positive Result
Sensory	Proprioception test	Assess the ability of the participant to detect the position of the great toe or ankle as it is moved by a researcher / clinician	Unable to detect changes in position
	Visual Vertical Test	Requires participant to orient a line to vertical and quantifies the deviation from vertical	Falls outside control group mean ± 2 SD
Ocular Motor	Saccadic Latency	Assesses the ability to make a rapid eye movement, latency would be the time it takes to initiate a saccade (eye movement) after the target has moved	Falls outside control group mean ± 2 SD
	Gaze	Assesses the ability to maintain stable vision on a fixed target.	
	Smooth Pursuit	Assesses the ability to accurately track/follow a moving/sinusoidal target with the eyes.	
	Convergence	Assesses the ability to view a close target without double vision	
Vestibular	cVEMP	Neurophysiological test assessing the function of the saccule	Falls outside control group mean ± 2 SD
	oVEMP	Neurophysiological test assessing the function of the utricle	
	Caloric	Assesses function of the lateral semi-circular canals and superior branch of the vestibular nerves	
	Head Impulse	Assesses function of semi-circular canals and vestibular nerve branches, specifically the lateral canals/superior vestibular nerve	

#### Statistical analysis

To determine if objective/novel measures of balance will better distinguish people with mTBI from control subjects than clinical measures, we will use logistic regression classification models. Improvements in classification will be determined by calculating the area under the curve (AUC) of the receiver-operator characteristic and then comparing AUC for each traditional clinical measure with the novel objective measures. Significance will be assessed using bootstrapping to determine if the observed differences in AUC are greater than would be expected by chance at a level of 0.05.

To determine if a subset of people with mTBI will have abnormal CSMI test measures, even without peripheral vestibular or ocular motor deficits, we will use descriptive statistics to characterize the distribution of CSMI test measures and vestibular/ocular motor scores. We will define CSMI test measures and vestibular/ocular motor scores as abnormal if the scores are greater than 2 standard deviations from the mean in controls. We will then classify mTBI subjects into one of 4 CSMI-vestibular/ocular motor categories 1) abnormal CSMI –abnormal vestibular/ocular motor scores, 2) abnormal CSMI –normal vestibular/ocular motor scores, 3) normal CSMI –abnormal vestibular/ocular motor scores, 4) normal CSMI –normal vestibular/ocular motor scores.

To determine if the observed relationship between poorer static/dynamic balance performance and mTBI is regulated/mediated by central sensorimotor integration, we will use mediation analysis. Mediation analysis [49] will allow for the partitioning of the association between mTBI and chronic imbalance into two parts, the direct relationship of mTBI on balance impairment as well as the causally mediated effect of mTBI on central sensorimotor integration, which, in turn is having the actual effect on imbalance. These varying generative mechanisms of balance deficits will be assessed by utilizing linear models relating mTBI to CSMI test measures alongside models of mTBI and CSMI test measures jointly affecting imbalance using the apportionment methods described by Baron and Kenny [49].

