**Methods:**

Two studies are described. Study 1 is a cross-sectional study to take place jointly at Oregon Health and Science University and the VA Portland Health Care System. The study participants will be individuals with non-resolving complaints of balance following mTBI and age- and gender-matched controls who meet all inclusion criteria. The primary outcome will be measures of central sensorimotor integration derived from a novel central sensorimotor integration test. Study 2 is a randomized controlled intervention to take place at Oregon Health & Science University. In this study, participants from Study 1 with mTBI and abnormal central sensorimotor integration will be randomized into two rehabilitation interventions. The interventions will be 6 weeks of vestibular rehabilitation 1) with or 2) without the use of an auditory biofeedback device. The primary outcome measure is the daily activity of the participants measured using an inertial sensor.

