### Participants

The study will include 65 mTBI participants and 65 control subjects for the cross-sectional arm of the study. All subjects will be between the ages of 18 and 60. Participants in the mTBI group will have a diagnosed mTBI or concussion and chronic, non-resolving complaints of balance problems determined by a score >0 on the Dizziness Handicap Inventory (DHI) at the time of testing and > 3 months post-injury. Control subjects will be gender and age matched to the mTBI group. For the second arm of the study, a subset of 40 mTBI subjects with abnormal central sensorimotor integration with or without peripheral vestibular or ocular motor deficits will be randomized into two rehabilitation groups, experimental treatment and standard of care, consisting of two rehabilitation sessions per week for 6 weeks. All subjects will be tested at either Oregon Health & Science University or the VA Portland Health Care System. All rehabilitation will take place at Oregon Health & Science University. Informed written consent will be obtained from all participants.

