#### Statistical analysis

To determine if ABF intervention improves central sensorimotor integration, we will build linear regression models to simultaneously evaluate the change in CSMI measures reflecting central sensorimotor integration and the effect of ABF compared to standard of care. Our outcome will be the change in pre- versus post-rehabilitation program CSMI measures; using the change (difference) in CSMI measures will control for the correlation of the repeated pre- and post- measures within an individual as well as maximizing the number of covariates we can potentially add into the regression models. Covariates of interest are vestibular/ocular motor scores, PTSD, Veteran versus civilian status, age, and gender. In addition, we will determine whether rehabilitation improved the static and dynamic balance metrics that were measured at the pre- and post-rehabilitation testing visits.

To determine if people with CSMI impairment show sustained improvement in static and dynamic balance after rehabilitation, even after ABF is discontinued, we will use linear mixed effects regression modeling which will include a third time point of interest (6 weeks after the rehabilitation intervention has stopped). Time will be treated as a categorical variable in order to evaluate changes in CSMI scores and balance during specific time periods, in this case, between the cessation of the intervention and the 6 weeks post-intervention follow-up. We will explicitly test the significance of a group by time interaction to determine if participants in the ABF rehabilitation group showed sustained improvements in outcomes beyond that experienced by participants with the standard of care. If applicable, we will then stratify the analysis by those with abnormal/normal measures of vestibular/ocular motor function to assess the relationship between vestibular/ocular motor function deficits and sustained improvement in CSMI score and balance.

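### Study 1 matches controls on age and gender, but its mediation models and AUC comparison, as written, leave both variables out

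*Protocol article*

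**What the plan says.** All references are to the protocol article.

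- **Design.** In Participants: "The study will include 65 mTBI participants and 65 control subjects for the cross-sectional arm of the study", and "Control subjects will be gender and age matched to the mTBI group". The abstract's Methods paragraph also says "age- and gender-matched controls who meet all inclusion criteria". No pairs, caliper or matching ratio are stated.
- **Classification (Study 1, Statistical analysis).** The tool is stated as "we will use logistic regression classification models". The test consists of "comparing AUC for each traditional clinical measure with the novel objective measures", with significance by bootstrap at 0.05.
- **Mediation (same section).** The approach is "utilizing linear models relating mTBI to CSMI test measures alongside models of mTBI and CSMI test measures jointly affecting imbalance".
- **Study 2, Statistical analysis.** "Covariates of interest are vestibular/ocular motor scores, PTSD, Veteran versus civilian status, age, and gender".

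Age and gender are thus named as matching factors for Study 1 and as covariates for Study 2, but they appear in no Study 1 analysis.

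**The concern.** Matching on age and gender makes the two groups alike on both, so neither can confound the mTBI-versus-control contrast. It does not remove their influence on the measurements within each group. Three things follow if the measures depend on age or gender.

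1. **Mediation path.** The link from CSMI to balance is estimated within groups. A variable that moves both creates an association there even if CSMI has no effect on balance. Hypothesis (c) rests on this path. The Discussion would use a positive result to direct rehabilitation towards central sensorimotor integration.
2. **Precision.** The spread due to age and gender stays in the residual variance of the mTBI-to-CSMI and mTBI-to-balance models. The precision that matching offers is not collected.
3. **AUC comparison.** The same spread pulls a pooled AUC towards 0.5, by an amount that differs between measures. This comparison decides hypothesis (a), and the Discussion would read a significantly larger AUC as showing that objective measurement is needed.

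**Working it through.** **The plan's own figure.** Study 1 states no AUC, AUC difference, mediation effect or power. Its 65 per group comes from a coefficient-of-variation target, bootstrapped from 12 pilot values that are not printed. There is nothing to reproduce for these analyses.

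**Inputs from the document:** 65 per group; matching on age and gender; two-sided 0.05 (the level is stated, the sidedness is my assumption).

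**Assumed input:** R², the share of a measure's within-group variance explained by the matching factors, shown from 0 to 0.30.

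**Step 1: precision of a group contrast.** With a balanced covariate and unit within-group SD, the unadjusted SE is √(2/65) = 0.175. The adjusted SE is 0.175 × √(1 − R²).

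| R² | Unadjusted SE | Adjusted SE | Ratio |
|---|---|---|---|
| 0.10 | 0.175 | 0.166 | 1.05 |
| 0.20 | 0.175 | 0.157 | 1.12 |
| 0.30 | 0.175 | 0.147 | 1.20 |

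**Step 2: the CSMI-to-balance path.** Suppose CSMI has no effect on balance, and the matching factors explain R² of each in the same direction. The within-group correlation is then r = √R² × √R² = R². With mTBI in the model, the residual df are 130 − 3 = 127, and the test statistic centres near r√127 / √(1 − r²). At R² = 0.10 this is 0.10 × 11.27 / 0.995 = 1.13.

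| R² in both | Centre of t | False-positive rate, formula | Simulated, unadjusted | Simulated, adjusted |
|---|---|---|---|---|
| 0 | 0 | 5% | 5% | about 5% |
| 0.05 | 0.56 | 9% | 10% | about 5% |
| 0.10 | 1.13 | 20% | 21% | about 5% |
| 0.20 | 2.30 | 63% | 62% | about 5% |
| 0.30 | 3.54 | 94% | 93% | about 5% |

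If the factors act on the two measures in opposite directions, r is negative and a real positive path can be masked. If they act on only one, r = 0 and there is no confounding.

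**Step 3: AUC.** For a binormal measure in groups with the same covariate distribution, pooled AUC = Φ(Φ⁻¹(A) × √(1 − R²)), where A is the age- and gender-specific AUC. For A = 0.80, Φ⁻¹(A) = 0.842. At R² = 0.10, 0.842 × 0.949 = 0.798, so the pooled AUC is 0.79. At R² = 0.30, 0.842 × 0.837 = 0.704, so it is 0.76.

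The comparison was simulated with 65 versus 65 and 3,000 replicates. Further assumptions: specific AUCs of 0.80 (objective) and 0.68 (clinical), correlation 0.3 between measures, and the DeLong standard error standing in for the bootstrap.

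| R² objective / clinical | Pooled difference | Power, pooled vs adjusted (pairs) | Power, pooled vs adjusted (group matching) |
|---|---|---|---|
| 0 / 0 | 0.119 | 63.1% vs 63.5% | 63.2% vs 63.0% |
| 0.3 / 0.3 | 0.108 (pairs), 0.107 (group) | 63.1% vs 63.3% | 63.5% vs 64.2% |
| 0.1 / 0 | 0.109 | 54.0% vs 64.8% | 54.1% vs 65.3% |
| 0.3 / 0 | 0.078 (pairs), 0.080 (group) | 26.9% vs 61.2% | 30.3% vs 64.4% |
| 0 / 0.1 | 0.129 | 69.1% vs 63.9% | 68.5% vs 65.3% |
| 0 / 0.3 | 0.149 (pairs), 0.148 (group) | 81.6% vs 65.7% | 79.1% vs 65.1% |

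In the last row the adjusted difference is about 0.12, so the extra power comes from an inflated difference. With both specific AUCs equal at 0.75, R² = 0.3 in the clinical measure alone gives a difference of 0.036 in favour of the objective measure and a rejection rate of 7.8% (pairs). With R² = 0.1 there, the difference is 0.009 and the rejection rate 4.7%.

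**The case against.** **Silence is not exclusion.** This is a condensed article, and covariate lists often sit in a fuller plan. The Study 1 text on clinical testing speaks of covariates that do not reappear in its analysis section, so that section is not exhaustive. This stands for the bootstrap's resampling unit, whose absence is no fault here. It carries less weight for the mediation models: their terms are written out, and the same article lists covariates for Study 2.

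**The pooled AUC is a legitimate target.** If a measure is to detect mTBI without regard to age or gender, the pooled AUC answers that question. This stands. An adjusted AUC is a different estimand and belongs beside the pooled one, not in its place.

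**Dependence on age or gender is not shown.** The age range is limited (18 to 60 in Participants, 21 to 50 in the inclusion criteria). Kp and Kd are normalised for anthropometrics, which may remove part of any gender effect. The clinical comparators include continuous measures such as gait speed, so nothing shows that the objective measures depend more on age. All of this stands, and it is why the sizes are conditional.

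**A stronger reading is tempting.** A reader might infer that the AUCs are necessarily understated, the standard errors too wide and the AUC comparison short of power. The document does not support that. Attenuation needs measures that depend on age or gender. For the AUC, too-wide standard errors appeared only with individual pairs (0.0418 estimated vs 0.0366 true at R² = 0.3; under group matching 0.0418 vs 0.0414), and Participants describes matching to the mTBI group without stating pairs. Power for the AUC difference can fall, stay the same or rise.

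**Conclusion.** The point holds in a conditional form. The Study 1 linear models, as written, omit the two variables used to build the control group, and the AUC comparison takes no account of them.

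The mediation path is the most exposed. If age and gender explain only 10% of both CSMI and balance in the same direction, a null path is declared significant about 21% of the time, and this does not depend on whether matching is individual. The loss of precision is modest: about 5% in the standard error at 10% explained and 20% at 30%. For the AUC comparison, the direction of bias is unknown. It vanishes if both measures depend equally on age and gender, and is small at 10% or less (about 0.01 in an AUC of 0.80), although power still moved by about 5 to 11 points when only one measure depended on them at 10%.

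None of these sizes can be computed from the document. They rest on the assumed shares of variance, AUCs and correlation in the working. The change is nonetheless worth making, because it costs little and protects the conclusion that depends on mediation.

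**What to change.** In Study 1, Statistical analysis:

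1. Add age and gender to every linear model: mTBI to CSMI, and mTBI plus CSMI to balance.
2. Keep the planned pooled AUCs. Beside them, as a sensitivity analysis, report age- and gender-adjusted AUCs: standardise each clinical and objective measure by a regression on age and gender fitted in the controls, then compare AUCs on the standardised values.
3. State whether matching is individual or by group, and resample by pair in the bootstrap only if it is individual.

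Both variables are already needed for matching, so no new data are required. The cost is about two degrees of freedom among 130 people, one extra set of AUCs, and a line labelling them as adjusted.

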The heterogeneity of balance deficits and varied rates of recovery after mTBI suggest varied etiologies and a need for interventions that address the underlying causes of poor balance function. Over-simplified clinical balance measures often do not account for the complex integration of sensory and motor systems. Therefore, the first goal of this study is to characterize balance deficits in people with mTBI who have chronic, non-resolving balance deficits compared to healthy control subjects without a history of mTBI. We hypothesize that a) objective measures of central sensorimotor integration, static and dynamic balance will better distinguish people with mTBI from control subjects than clinical measures, b) a subset of people with mTBI will have abnormal central sensorimotor integration test measures, even without peripheral vestibular or ocular motor deficits, and c) the relationship between poorer static/dynamic balance performance and mTBI is regulated/mediated by central sensorimotor integration. The second goal is to determine if augmenting a traditional balance rehabilitation program with a wearable-sensor based ABF system improves central sensory integration in patients with chronic mTBI compared to the standard balance rehabilitation program. Our central hypothesis is that chronic balance deficits after mTBI result from impairments in central sensorimotor integration that may be helped by rehabilitation that challenges balance while simultaneously providing feedback on balance performance. We hypothesize that a) central sensorimotor integration scores will improve with rehabilitation and ABF will increase the improvement of central sensorimotor integration scores beyond the standard of care, b) intervention with ABF will improve objective measures of balance and c) people with central sensorimotor integration impairment will show sustained improvement in central sensorimotor integration scores and balance after rehabilitation with ABF.

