## Discussion

The goal of this study is to determine whether persistent balance and gait deficits following mTBI are attributable to improper central sensorimotor integration and to examine the potential for augmented rehabilitation to improve daily activity levels. In particular, this study is unique in its investigation of central sensorimotor integration in people with persistent balance complaints following mTBI in that confounding covariates such as vestibular disruption, neurocognition, and physical activity will be objectively quantified. Additionally, if we find that the quantitative balance, gait, or novel CSMI measures have a significantly greater AUC compared to the clinical measures (BESS, gait speed, SOT) at detecting patients with chronic mTBI, this will indicate the necessity for objective quantification of gait and balance deficits for mTBI assessment.

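### Study 1 tests many clinical-versus-objective AUC differences at one undivided 0.05 with no main comparison, so the error rate of its superiority claim depends on choices the text leaves open

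*Protocol article*

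**What the plan says.** The first hypothesis of Study 1, at the end of the Background, concerns objective measures as a class: "objective measures of central sensorimotor integration, static and dynamic balance will better distinguish people with mTBI from control subjects than clinical measures". Study 1, Statistical analysis, sets the method: "we will use logistic regression classification models", followed by "comparing AUC for each traditional clinical measure with the novel objective measures". The test is a bootstrap of the AUC differences, and the criterion is that they be "greater than would be expected by chance at a level of 0.05". The differences are plural and the level is single. No pair or model is named as the main one.

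The Discussion gives the decision rule. If "the quantitative balance, gait, or novel CSMI measures have a significantly greater AUC compared to the clinical measures (BESS, gait speed, SOT"), the authors will take objective quantification of gait and balance to be necessary for assessing mTBI. The objective side of that rule is joined by an explicit or. On the clinical side it names three comparators without saying whether one or all must be beaten.

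On size: "The study will include 65 mTBI participants and 65 control subjects". The Study 1 Sample size section derives this from the coefficient of variation of Kp in pilot controls, not from an AUC difference.

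**The concern.** Several routes lead to one strong claim, and each route is tested at the full 0.05. If the objective measures are in truth no better than BESS, gait speed and SOT, the chance that the study still declares them better is not the stated level.

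Two mechanisms could raise it, and they belong to different readings of the plan:

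- **Measures compared one at a time.** The error comes from the number of comparisons. Fitting a one-predictor logistic model adds almost nothing, because the AUC depends only on ranks and direction.
- **Objective measures combined in one model.** Few comparisons remain, but the model's apparent AUC is inflated by overfitting relative to a single clinical measure, unless it is validated.

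At stake is the conclusion on hypothesis (a) of Study 1.

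**Working it through.** **Inputs from the article.** 65 cases and 65 controls (Participants); level 0.05 (Study 1, Statistical analysis); three clinical comparators (Discussion). Instrumented balance and gait outputs in Table 3, each counted once: modified BESS 5, CTSIB 1, single-task gait 5, dual-task change 5, turning 3, fast turning 3, so 5+1+5+5+3+3 = 22. Table 2 adds 7 CSMI parameters, giving 22+7 = 29. Counting CSMI values per test (one fitted weight plus Kp, Kd, Kt and td, in 8 tests) gives 5×8 = 40, and 22+40 = 62.

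**Assumptions, not in the article.** Two-sided test, so 2.5% in favour of the objective measure. All measures have the same true AUC (0.65 unless stated), with normal scores shifted by d = √2·Φ⁻¹(AUC). Correlation is 0 to 0.8 between single measures and 0 in joint models.

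**Step 1: the plan's own figure.** For one paired comparison, Z = (AUC_obj − AUC_clin)/√(V_obj + V_clin − 2C), with DeLong variances. Two-sided rejection averages 0.051 over 12 runs of 800. A paired percentile bootstrap gives 0.048 and 0.070 in 400 trials each. So 0.05 is about right for one comparison.

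**Step 2: bound for independent tests.** 1 − 0.95^21 = 0.659 for 3×7 pairs and 1 − 0.95^87 = 0.988 for 3×29. Counting only one direction, 1 − 0.975^21 = 0.412 and 1 − 0.975^87 = 0.889. These overstate the risk, because pairs share measures.

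**Step 3: measures compared singly, simulated with their dependence** (Z > 1.96 counts as superiority; three clinical comparators):

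| Objective measures | True AUC | Any beats any clinical | One beats all three |
|---|---|---|---|
| 3 | 0.68 | 15–19% | see below |
| 7 | 0.65 | 26–29% | 0.6–1.3% |
| 7 | 0.68 | 22–28% | see below |
| 22 | 0.68 | about 51% | see below |
| 29 | 0.65 | 51–57% | 3.1–4.0% |

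The runs at 0.68 gave about 0.3–5% for beating all three. Runs at true AUC 0.70 gave 21–25% (6 measures), 46–52% (22) and 63–69% (62) for any-beats-any, and 0.3–9% for beating all three, the upper end with 62 measures. The assumed correlation hardly matters. If all ten clinical balance, gait and SOT outcomes in Table 3 count as comparators (BESS 1, CTSIB 1, single-task gait 2, dual-task 1, turning 1, fast turning 1, SOT 3), any-beats-any with 29 objective measures is 85–87%.

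**Step 4: joint model, AUC taken on the fitting data, against one clinical measure of equal true AUC 0.65** (500 runs, one informative predictor):

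| Predictors | Mean apparent AUC | False superiority |
|---|---|---|
| 1 | 0.65 | 2.4% |
| 7 | 0.70 | 8.2% |
| 15 | 0.74 | 27.2% |
| 29 | 0.81 | 74.2% |

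Replacing DeLong by a percentile bootstrap of the difference gives 7%, 23% and 74% for 7, 15 and 29 predictors on fixed scores. Refitting in each resample without optimism correction gives 15%, 63% and 100%. A plain bootstrap therefore does not remove the inflation. Requiring the joint model to beat all three clinical measures (true AUC 0.65–0.70, 600 runs) gives about 1% with 7 predictors, 16–25% with 22 and 78–86% with 40.

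**Step 5: do the remedies work?** Bonferroni over all pairs (0.05/21 = 0.0024; 0.05/87 = 0.0006) brings any false objective superiority to 2.1–2.8% and 1.0–2.9%. With 10-fold cross-validated AUC, a joint model falsely beats one clinical measure in at most 2.7% of runs at every size tried.

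**The case against.** The strongest reply is that this is an ambiguity, not an established error.

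- **All three comparators.** The Discussion names three clinical measures, and the analysis section speaks of each one. Requiring superiority to all of them is at least as natural a reading. With single measures the risk is then about 5% or less for up to about 29 measures. This stands. A reader might infer that false superiority is likely however the plan is read; it is not.
- **Where the AUC is computed.** A reader might infer that the AUC is taken on the data that fitted the model. The article does not say so. It describes no validation and mentions the bootstrap only as the significance test, but as a condensed article it may leave validation to the full protocol or SAP. The overfitting figures are therefore conditional.
- **Large models and counts.** Nothing in the text plans a 40-predictor model or 62×3 comparisons. The or in the Discussion joins three domains. This stands, but 3 objective measures already give 15–19% if any one clinical measure suffices.
- **The bootstrap might absorb overfitting.** A scheme built for that could. The article names none, and the percentile versions tried did not.
- **Study 1 is descriptive.** In part it is. But this comparison is a stated hypothesis with a significance level and a firm conclusion attached, so its error rate matters.

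What survives does not rest on missing SAP detail: the single undivided level, the unnamed main comparison and the or in the conclusion are all in the text.

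**Conclusion.** The point holds in conditional form. The written rule does not fix the error rate of the Study 1 superiority claim, and some natural readings put it far above the stated level. With single comparisons where any one clinical measure suffices, false superiority is about 15–30% with 3–7 objective measures and about 50% with 22–29. If one measure must beat all three, it is about 5% or less for up to about 29 measures, and up to 9% with 62. With a joint model and no validation, it is about 7–8%, 23–27% and 74% with 7, 15 and 29 predictors, against 2.5% intended.

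Multiplicity and overfitting are alternatives and should not be added together. The sizes rest on equal true AUCs of 0.65–0.70, on how the measures are counted and on a two-sided test, none of which the article fixes. The documents do not support saying that every reading breaks 0.05: single measures with an all-three requirement, or small or validated joint models in a restricted set of comparisons, stay near it.

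**What to change.** In Study 1, Statistical analysis:

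1. State whether objective measures enter singly or jointly, and whether one or all of BESS, gait speed and SOT must be beaten.
2. Name one main comparison, for example one prespecified CSMI model against those three, requiring superiority to all three or using Holm. Alternatively, use a bootstrap max-statistic over all AUC differences so that 0.05 covers the whole claim. Call all other pairs descriptive.
3. For any multi-measure model, compare cross-validated or optimism-corrected AUCs, with the model refitted in each resample.

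In the Discussion, tie the conclusion about objective measurement to that main comparison.

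The cost is a few sentences and some computing, with no added participants or visits. Reported AUC gains will be smaller, and secondary pairs will have less power.
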